### Statistical analysis

SAS version 9.1.3 will be used for data analysis (SAS Institute Inc., Cary, NC). Descriptive statistics of participant baseline characteristics will be presented for each treatment group to assess their comparability as well as the generalizability of the sample. We will use an intention-to-treat approach for all analyses. The analyses for the primary and secondary aims are described below. We will not impute any missing data for analysis, but will report the amount of missing data for each variable and the reason it is missing.

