#### Treatment Allocation

A web programmer wrote the code and a data manager validated the code for an adaptive computer-generated treatment allocation algorithm based on the minimization method of Taves to allocate participants to one of three treatment groups in a 1:1:1 allocation ratio [74]. The minimization algorithm balances group differences over 3 baseline factors: age (21-39; 40-49; 50-65), sex and duration of pain ( < 4 weeks; 4-12 weeks; 12 weeks- < 6 months; 6 months- ≤ 1 year; > 1 year). The study coordinator selects the participant unique identification (ID) number from a dropdown list in a web-based interface that produces the coded treatment group allocation. The date and time of allocation, study personnel user ID and group assignment are stored in the project database. All study personnel are blinded to upcoming treatment allocations and the biomechanical examiners remain blinded to treatment group throughout the study. If the web system becomes unavailable due to server failure, a back-up treatment allocation protocol is administered with predetermined sequentially numbered, opaque envelopes stored in a locked cabinet in a secure area. Subsequent allocations via the minimization algorithm take into account all participants' minimization variables.

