### Sample size justification

We calculated power using Proc Power in SAS for a total sample size of 219 by considering 63 patients per group and inflating that by 15% (73 per group) to account for drop outs. Because we anticipate no drop outs during BL2, we considered 73 per group in the power analyses for the immediate changes in the pre to post treatment measurements at the first treatment, but 63 per group for the changes in the pre-treatment variables at BL2 and week 2.

We conducted power analyses for the 3 standing postural sway characteristics, mean sway away from the center in the X and Y directions and the mean planar sway speed. These are the primary response variables and we estimated power using changes in similar variables collected from participants standing on a solid force plate, described previously, in the literature and standard deviations from our preliminary studies [47,94]. Table 3 presents a variety of power values for these variables.

**Table 3 T3:** Statistical power based on one-way ANOVA for the 3 primary response variables testing at 0.05 level of significance using SDs from preliminary data and the literature

		Power A	Power B
		
Response Variable		Contrasts*	Contrasts*
Sway Speed	Solid	>99%	>99%
	
	Foam	86	80

Mean Sway X	Solid	76-94	69-90
	
	Foam	64-73	58-67

Mean Sway Y	Solid	88-95	83-92
	
	Foam	21-34	18-30

Effect sizes: Sway Speed: 4 mm/sec; Mean Sway X: 1 mm; Mean Sway Y: 0.5 mm [47,94] Power A is determined for n = 73 per group for the immediate changes in the pre- to post-treatment measurements at the first treatment. Power B is determined for n = 63 per group for the changes in the pre-treatment variables at the first treatment and at week 2.

*Two 1 degree of freedom contrasts to test mean differences of HVLA-SM vs Sham Control and LVVA-SM vs Sham Control.

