#### Data Analysis for Primary Aim

For each of the 3 primary response variables, the immediate changes in the pre to post treatment measurements at BL2 and the changes in the pre-treatment variables from BL2 to week 2 will be compared across the 3 treatment groups using analysis of covariance (ANCOVA) adjusting for the minimization variables. The following 2 preplanned contrasts for the 2 degrees of freedom for treatment will be tested at 0.05: HVLA-SM vs. sham control and LVVA-SM vs. sham control on the adjusted means based on the ANCOVA model. Residual plots will be used to assess the adequacy of the model assumptions. Data transformations will be explored when model assumptions are violated. Further adjustments for the following baseline characteristics will be explored to increase the precision of the estimated effects: RMDQ, NRS, Quebec Task Force classification, Beck Depression Inventory and chiropractic care (yes/no). Adjusted group means and mean differences between SM and control groups will be reported with 95% confidence intervals determined under the final ANCOVA model.

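### The 2-week primary sway comparison is labelled intention-to-treat but leaves out everyone without a week-2 value, and is biased if drop-out is response-related and differs between arms

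*Protocol article*

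**What the plan says.** The Statistical analysis section sets the principle, "We will use an intention-to-treat approach for all analyses", and the missing-data rule, "We will not impute any missing data for analysis". The only other provision there is to report how much is missing and why.

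Under Data Analysis for Primary Aim, the second primary comparison is fixed: "the changes in the pre-treatment variables from BL2 to week 2 will be compared across the 3 treatment groups", by ANCOVA adjusted for the minimization variables. Treatment Allocation lists these: "The minimization algorithm balances group differences over 3 baseline factors: age (21-39; 40-49; 50-65), sex and duration of pain". Sway is not among them, nor among the further baseline covariates to be explored.

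Sample size justification sets the numbers by "considering 63 patients per group and inflating that by 15% (73 per group) to account for drop outs". It uses 73 per group for the immediate BL2 comparison, where no drop-out is expected, and 63 per group for the change to week 2.

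**The concern.** A change score at one time point exists only for people measured at both visits. With imputation excluded and no other model stated, a participant lost before week 2 cannot enter the comparison. The analysis is then one of observed cases, under a label that most readers take to mean everyone allocated.

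The plan also holds useful data on those it leaves out. Sway is measured before and after treatment at BL2 (Sensorimotor Function Tests; Table 2), so someone who leaves before week 2 will normally have a baseline value and a response to the first allocated treatment. Neither is used.

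At stake is the only primary comparison of repeated treatment with sham. The sham arm moves to active manipulation after week 2 and the plan has no control group at 6 weeks, so a distorted 2-week contrast cannot be checked later in the trial.

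**Working it through.** **Inputs from the protocol article.** 73 allocated and 63 counted at week 2 per group; 15% inflation; contrasts tested at 0.05 (taken as two-sided); planned effects of 4 mm/sec (sway speed), 1 mm (Mean Sway X) and 0.5 mm (Mean Sway Y); the power values in Table 3. The article gives no standard deviations, no correlations between sway measurements and no difference between completers and drop-outs. These are assumed below.

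**1. The plan's own figures.** 63 × 1.15 = 72.45, rounded up to 73; 3 × 73 = 219. This matches the stated sample size. Solving each Power A value for the standardised effect at n = 73 and recomputing at n = 63 returns all nine numeric Power B values within 1 point (sway speed on foam: 80.6% against 80%; X solid: 69.7-90.4% against 69-90%). The 2-week power therefore rests on 63 observed participants per arm.

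**2. Share left out.** (73 − 63)/73 = 10/73 = 13.7% per arm; 219 − 3 × 63 = 30 of 219 in total.

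**3. Size of bias by arithmetic.** Bias in one arm = share missing × (mean change in completers − mean change in drop-outs). If that gap equals the whole planned effect in one arm and is zero in the other, the contrast shifts by:
- sway speed: 0.137 × 4 = 0.55 mm/sec
- Sway X: 0.137 × 1 = 0.14 mm
- Sway Y: 0.137 × 0.5 = 0.07 mm

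That is 14% of the planned effect. A gap of a quarter of the effect gives about 3%. Full-size gaps in opposite directions double 13.7% to 27%. Equal gaps at equal rates in both arms cancel.

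**4. Size of bias by simulation.** Assumptions: no true effect, 73 per arm, 13.7% drop-out, sway correlations 0.6-0.8, drop-out driven by the immediate response at BL2 with log-odds of 1 per SD.

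| Drop-out mechanism | Bias (SD of change) | Type I error |
|---|---|---|
| Related to response, one arm only | 0.06-0.07 | 6-7% |
| Related to response, opposite directions | up to 0.13-0.16 | 11-16% |
| Related to response, same in both arms | 0 | about 5% |
| Unrelated to response | 0 | about 5% |

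Other correlation patterns within 0.6-0.8 give less: 0.04-0.06 SD for one arm and 0.09-0.13 SD for opposite selection.

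Analytic check: with 63 per arm the standard error is √(2/63) = 0.178 SD. A bias of 0.07 SD is 0.39 standard errors and gives rejection in about 7%. A bias of 0.13 SD is 0.73 standard errors and gives about 11%.

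**5. Against the planned effects.** Table 3 implies standardised effects of about 0.39-0.60 for Sway X and for Sway Y on the solid surface. One-arm selection is then 0.06/0.60 = 10% to 0.07/0.39 = 18% of the effect. Opposite selection at its upper values is 0.13/0.60 = 22% to 0.16/0.39 = 41%.

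**6. What a likelihood model recovers.** With BL2 pre-treatment, BL2 post-treatment and week-2 sway as responses, bias is essentially nil when drop-out depends on BL2 sway. That follows from the set-up, because the driver is in the model. If drop-out instead follows an unmeasured variable correlated 0.5 with the sway change, roughly 60-80% of the bias remains.

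**The case against.** Four arguments limit the point.

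- **Meaning of the label.** Intention-to-treat can mean only that participants are analysed in the arm to which they were allocated. The no-imputation rule stands beside it and the smaller n is disclosed, so nothing is hidden. This is fair as to candour. It does not change who enters the comparison.
- **No evidence of informative drop-out.** A reader might infer that the 2-week result will be biased. The article does not support that. Participants stand blindfolded on a force plate, and nothing says that they are told their sway result. The sham lasts 2 weeks and active manipulation follows, which is a reason to stay. The 13.7% is a planning allowance, not an observed loss. This stands: the bias is conditional, and modest unless the arms differ markedly in who leaves.
- **Limits of the remedy.** A reader might infer that a mixed model abolishes the bias. It does not if drop-out follows pain or perceived benefit that the model does not capture. This also stands, and is a reason to add baseline pain and disability.
- **Left to an analysis plan.** Sensitivity analyses for missing data often are, and their absence here is no finding. But this article itself fixes the model, the no-imputation rule and the label, and the point concerns those three.

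It would also be wrong to extend the point to both primary aims: no drop-out is expected within BL2. Nor is this the only comparison of repeated treatment with sham, because a secondary aim makes it for sudden load and repositioning.

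**Conclusion.** The point holds in a limited form. By the plan's own rules, the 2-week primary sway comparison omits about 10 of 73 participants per arm (13.7%) and ignores their BL2 sway, which does not fit an intention-to-treat label applied to all analyses.

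The harm is conditional. Response-related drop-out in one arm only would cost about 0.06-0.07 SD and raise type I error to 6-7%. Opposite selection could reach about 0.13-0.16 SD and 11-16%. These figures rest on the planned drop-out rate, assumed correlations of 0.6-0.8 and an assumed drop-out mechanism. Drop-out that is unrelated to response, or that works alike in both arms, leaves the contrast unbiased.

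The change is worth making because it is cheap and uses data already collected.

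**What to change.** For the 2-week endpoint, make the primary analysis a likelihood-based repeated-measures model on all allocated participants:

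- responses: BL2 pre-treatment, BL2 post-treatment and week-2 pre-treatment sway
- terms: arm-by-time, the minimization factors, and baseline NRS and RMDQ (both already collected)
- unstructured covariance
- the two planned contrasts on the BL2-to-week-2 change, estimated from this model
- the missing-at-random assumption, stated in the text

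Keep the change-score ANCOVA as a sensitivity analysis and label it as observed cases. The immediate BL2 analysis can stay as planned.

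The cost is a change of wording and one mixed model per sway variable. No new data are needed, and nothing is imputed, so the plan's own rule is kept. The downside is that the model reduces but does not remove bias if drop-out depends on values that were not observed.

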To enable comparison between participants, an EMG normalization procedure is performed. The participant lays face down on a bench, with upper trunk extending out over the front edge and supported by the elbows. The legs are strapped to the table at the buttocks and at the ankles. EMG is recorded when the participant lifts their elbows off the support using their back muscles and holds the posture for 5 seconds. EMG is also recorded for 5 seconds before the lifting and for another 5 seconds after the participant places their elbows back to the support. If the participant reports an increase in pain during the pre-treatment lifting phase, the normalization procedure is discontinued. In that case, the post-treatment normalization and sudden load tests are also not conducted. If there is no increase in pain before the treatment, but there is during the post-treatment normalization lifting phase, both the post-treatment normalization and sudden load tests are discontinued.

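### The 2-week primary comparison is labelled intention-to-treat but is a complete-case analysis, planned to omit about 10 of 73 participants per arm

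*Protocol article*

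**What the plan says.** Three statements in the protocol article bear on the week-2 comparison.

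- **Statistical analysis** gives the label: "We will use an intention-to-treat approach for all analyses". The same section rules out imputation: "We will not impute any missing data for analysis". It commits instead to stating, variable by variable, how much is missing and why.
- **Data Analysis for Primary Aim** fixes the model. For each of the three sway variables, "the changes in the pre-treatment variables from BL2 to week 2 will be compared across the 3 treatment groups using analysis of covariance (ANCOVA"). The covariates are the minimization variables, which **Treatment Allocation** lists as age, sex and duration of pain. Further baseline characteristics, including pain and disability scores, are only to be explored, and for precision.
- **Sample size justification** obtains its 219 by "considering 63 patients per group and inflating that by 15% (73 per group) to account for drop outs". It uses 73 per group for the immediate BL2 change, where no dropout is expected, and 63 per group for the change to week 2.

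For the secondary sensorimotor outcomes, **Response to Sudden Load** says that if pain first increases during the lifting phase of the EMG normalization after treatment, "both the post-treatment normalization and sudden load tests are discontinued". Testing also stops if pain increases at the mock drop. **Repositioning Accuracy** drops target positions, or the whole test, when pain increases. **Data Analysis for Secondary Aim a** applies the primary model to these outcomes, reporting estimates and 95% confidence intervals without P-values.

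**The concern.** A change score needs both of its values. With no imputation and one score per participant, the week-2 ANCOVA is fitted to completers. The intention-to-treat label is correct in that people stay in their allocated arm. It is not correct if the reader takes it to mean that everyone allocated contributes. The plan states no assumption under which the completer contrast estimates the effect for all those allocated.

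That assumption matters here. The model conditions only on arm, age, sex and pain duration. Pain intensity and disability could plausibly influence who leaves a back pain trial, but they are not in the fixed covariate set, and neither is baseline sway. One arm receives sham for the two weeks, so dropout could differ by arm. The post-treatment sway value at BL2 is scheduled for everyone (Table 2) but does not inform the week-2 comparison.

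A narrower version applies to the immediate changes in sudden-load response and repositioning. Some post-treatment values are missing because pain increased during the post-treatment testing. Treatment may affect whether that happens, so the contrast is conditional on tolerating the test.

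**Working it through.** **1. The plan's own sample size.** Inputs from Sample size justification: 63 evaluable per group, 15% inflation, three groups.

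- 63 × 1.15 = 72.45, rounded up to 73; 3 × 73 = 219. The stated figures reproduce.
- (Dividing instead, 63 / 0.85 = 74.1, so 75. A true 15% loss from 73 leaves 73 × 0.85 = 62.05. Either way the result is within two patients per group and is not the issue here.)

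**2. Is the week-2 power a completer power?** Table 3 gives no SDs, so the standardized effect d was solved from each Power A value (n = 73) and power recomputed at n = 63. Assumptions: two-sided 0.05 and a 1-df contrast in a three-group ANOVA, using a noncentral t with 3(n − 1) df and noncentrality d√(n/2).

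| Row in Table 3 | Power A | d | Recomputed at 63 | Stated Power B |
|---|---|---|---|---|
| Sway speed, foam | 86 | 0.505 | 80.6 | 80 |
| X, solid (low) | 76 | 0.443 | 69.7 | 69 |
| X, solid (high) | 94 | 0.584 | 90.4 | 90 |
| X, foam (low) | 64 | 0.385 | 57.6 | 58 |
| X, foam (high) | 73 | 0.428 | 66.6 | 67 |
| Y, solid (low) | 88 | 0.521 | 82.9 | 83 |
| Y, solid (high) | 95 | 0.599 | 91.7 | 92 |
| Y, foam (low) | 21 | 0.192 | 18.7 | 18 |
| Y, foam (high) | 34 | 0.257 | 30.0 | 30 |

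All nine solvable pairs agree within one percentage point. Power B is therefore power with the dropouts removed, so the plan itself expects them to be absent from the week-2 analysis.

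**3. Planned omission.** (73 − 63) / 73 = 10/73 = 13.7% per arm; 3 × 10 = 30 of 219.

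**4. Size of a possible shift.** Let m be the missing fraction in an arm and g the completer mean change minus the unseen dropout mean change, in SD units. The completer mean exceeds the all-allocated mean by m × g. For a contrast of arm 1 with arm 0:

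shift = m₁g₁ − m₀g₀

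The document gives no value for g, so the following are assumptions.

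- Loss in one arm only, m₁ = 0.137: g = 0.25 gives 0.034 SD; g = 0.5 gives 0.069 SD; g = 1 gives 0.137 SD.
- Against the effect implied for sway X on the solid surface, g = 0.5 and g = 1 amount to 15% and 31% of 0.443 SD (low end), or 12% and 23% of 0.584 SD (high end).
- Equal loss and equal g in both arms: shift = 0.

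**5. Which comparisons are touched.**

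- Immediate BL2 change in sway: no dropout is anticipated and 73 per group is used, so it is not affected by this route.
- BL2-to-week-2 change in sway: complete-case, as above.
- Stopping during post-treatment sudden-load or repositioning tests: this removes post-treatment values, so it affects the immediate change. The BL2-to-week-2 change uses pre-treatment values only.

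**The case against.** The strongest reply has four parts.

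*Intention-to-treat often means only analysis by allocated group, and missing-data sensitivity analyses belong in an analysis plan that is not shown.* The first half is fair, and the plan does meet that narrower meaning. But the article itself fixes the label, the model and the ban on imputation. A later document could add sensitivity analyses; it could not add imputation without contradicting the article.

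*The plan is open about missing data.* It commits to reporting the amount and reasons, and **Data collection and management** records losses to follow-up and completers. This stands. Tests stopped for pain should therefore appear with their reason, although a comparison by arm with an interval is not stated. Reporting reasons does not change the estimate.

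*The bias is hypothetical.* This also stands. The plan allows the same loss in every arm, and symmetric loss with symmetric differences cancels. Sham participants move to doctor's choice manipulation after week 2, which gives them a reason to stay until then. A reader might infer that the week-2 result will be biased, or that 15% of participants are excluded. The documents support neither: a completer analysis can be unbiased, and the allowance is a planning figure that works out at 13.7% of those allocated.

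*The sudden-load stopping rule concerns pain provoked by testing.* Correct. A reader might infer that it removes the participants whom treatment made worse and so conceals harm. The rule responds to pain during a trunk-lifting manoeuvre or a mock drop, which is not the same as worsening from treatment. The outcome is secondary and reported without P-values. Adverse events are probed for at each visit and recorded separately (**Safety Monitoring**, **Adverse Events**). What remains is that the immediate contrast is conditional on tolerating the test.

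**Conclusion.** The point holds for the week-2 primary comparison. As written, it is an analysis by allocated group among completers, planned to leave out about 10 of 73 per arm, and the unqualified intention-to-treat label does not describe it. Its validity rests on an unstated assumption: missingness at week 2 is unrelated to sway change once arm, age, sex and pain duration are taken into account.

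The documents establish the mechanism and the planned omission. They do not establish a bias. The 0.07 to 0.14 SD figure describes one assumed scenario, with loss confined to one arm and dropouts differing by 0.5 to 1 SD, and should be read only as showing that the question is not negligible beside the effects the trial is powered for. For sudden load and repositioning, the point is limited to how the immediate secondary contrasts are interpreted.

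**What to change.** - **Week-2 primary analysis.** Use a constrained longitudinal mixed model of all allocated participants, with BL2 pre-treatment, BL2 post-treatment and week-2 pre-treatment sway as outcomes: common baseline mean across arms, unstructured covariance, minimization factors as covariates, and the same two contrasts at week 2. It is likelihood-based, so it respects the ban on imputation, and it uses only measurements already scheduled.
- **Sensitivity analysis.** Keep the planned change-score ANCOVA and describe it as analysis by allocated group among completers.
- **Assumption.** State missing-at-random explicitly. The model removes bias only so far as the BL2 values predict both dropout and week-2 sway. Both are taken on the day of the first treatment, so they cannot reflect a lack of improvement that develops later.
- **Sudden load and repositioning.** Leave the safety rule untouched. Report by arm, with a 95% confidence interval, the proportion stopped for increased pain, and say that the immediate contrast applies to those who tolerated the test.

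The cost is revised wording and modest programming, with no new data collection. The downsides are slightly more complex reporting and reliance on missing-at-random.

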#### Data Analysis for Primary Aim

For each of the 3 primary response variables, the immediate changes in the pre to post treatment measurements at BL2 and the changes in the pre-treatment variables from BL2 to week 2 will be compared across the 3 treatment groups using analysis of covariance (ANCOVA) adjusting for the minimization variables. The following 2 preplanned contrasts for the 2 degrees of freedom for treatment will be tested at 0.05: HVLA-SM vs. sham control and LVVA-SM vs. sham control on the adjusted means based on the ANCOVA model. Residual plots will be used to assess the adequacy of the model assumptions. Data transformations will be explored when model assumptions are violated. Further adjustments for the following baseline characteristics will be explored to increase the precision of the estimated effects: RMDQ, NRS, Quebec Task Force classification, Beck Depression Inventory and chiropractic care (yes/no). Adjusted group means and mean differences between SM and control groups will be reported with 95% confidence intervals determined under the final ANCOVA model.

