### Sensorimotor Function Tests

The sensorimotor function tests applied in this study include postural sway, lumbar repositioning accuracy, and response to sudden load. The participant performs one set of these tests immediately before the treatment and another set immediately after the treatment at the BL2, week 2 and week 6 visits (up to six sets of sensorimotor function tests in total). The detailed order of the tests is illustrated in Figure 2.

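### The primary ANCOVA of sway change omits the pre-treatment sway value: the contrast is valid but avoidably imprecise

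*Protocol article*

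**What the plan says.** Under Data Analysis for Primary Aim, the protocol article fixes the outcome as "the immediate changes in the pre to post treatment measurements at BL2 and the changes in the pre-treatment variables from BL2 to week 2". These are compared across the three groups "using analysis of covariance (ANCOVA) adjusting for the minimization variables". Treatment Allocation names those variables: "The minimization algorithm balances group differences over 3 baseline factors: age (21-39; 40-49; 50-65), sex and duration of pain".

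The primary-aim section then lists further covariates: Roland-Morris score, pain rating, Quebec Task Force class, Beck Depression Inventory and chiropractic care. Adjustment for these "will be explored to increase the precision of the estimated effects". The pre-treatment value of the sway outcome is in neither list.

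That value exists for the purpose. Under Sensorimotor Function Tests, "The participant performs one set of these tests immediately before the treatment and another set immediately after the treatment" at BL2, week 2 and week 6. Data Analysis for Secondary Aim a carries the same model to the remaining sensorimotor variables.

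**The concern.** A change score subtracts the baseline with its coefficient fixed at 1. If pre and post values are imperfectly correlated, that coefficient is usually too large. Participants with high sway before treatment then tend to show a fall whatever they receive, and this spread goes into the error term. Putting the baseline value in the model lets the data choose the coefficient.

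Precision is at stake. Table 3 of the article puts several primary contrasts below 80% power, so a free gain is worth having. The allocation does not help here, because sway is not one of the minimization factors and a chance difference in baseline sway between arms is left to the analysis.

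**Working it through.** **Inputs from the article.** Change-score outcome, covariate lists, 73 per group (Power A) and 63 per group (Power B), effect sizes of 4 mm/s, 1 mm and 0.5 mm, and the Table 3 powers. "The following 2 preplanned contrasts for the 2 degrees of freedom for treatment will be tested at 0.05"; I take this as two-sided. **Not given:** the SDs and the pre/post correlation r. I assume r = 0.5, 0.8 and 0.9.

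**1. The article's own figures.** 63 × 1.15 = 72.45, rounded up to 73; 3 × 73 = 219, as stated. For power I used a 1-df contrast in a three-group ANOVA (noncentral t, 3n − 3 df), solved for the SD that gives each Power A at n = 73, and predicted Power B at n = 63:

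| Contrast | Power A | Power B predicted | Power B stated |
|---|---|---|---|
| Sway speed, foam | 86 | 80.6 | 80 |
| X, solid, low end | 76 | 69.7 | 69 |
| X, foam, low end | 64 | 57.6 | 58 |
| Y, foam, high end | 34 | 30.0 | 30 |

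Every finite Power B value follows within 0.7 points. Table 3 is therefore internally consistent as a covariate-free calculation. Its absolute level cannot be checked without the SDs.

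**2. Variance ratio.** With equal pre and post SD s:

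- Var(change) = 2s²(1 − r)
- Var(baseline-adjusted) = s²(1 − r²)
- Ratio = (1 + r)/2 = 0.75, 0.90, 0.95 at r = 0.5, 0.8, 0.9

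The variance falls by 25%, 10% and 5%. The change-score analysis would need 1/ratio times the sample for the same precision: 33%, 11% and 5% more participants. A simulation of 8,000 trials with 3 × 73 participants gave ratios of 0.740 at r = 0.5 (theory 0.75) and 0.963 at r = 0.9 (theory 0.95).

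With unequal SDs the excess variance of the change score is (s_pre − r·s_post)². This is never negative, and it is zero when r = s_pre/s_post.

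**3. Power B after adjustment.** I treated the Table 3 SDs as SDs of change, solved the standardized effect from the stated Power B, and divided it by √ratio:

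| Contrast | Stated | r = 0.5 | r = 0.8 | r = 0.9 |
|---|---|---|---|---|
| X, solid, low end (effect 0.44 SD) | 69 | 81 | 74 | 71 |
| X, foam | 58–67 | 70–79 | 63–72 | 60–69 |
| Sway speed, foam | 80 | 90 | 84 | 82 |

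**4. Where the excess variance comes from.** Under equal variances, 2s²(1 − r) − s²(1 − r²) = s²(1 − r)². This is the contribution of chance baseline imbalance. Given a realised baseline difference D between two arms, the change-score contrast shifts by −(1 − r)D. The simulated slopes were −0.51 at r = 0.5 and −0.09 at r = 0.9, against about 0 after adjustment.

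Take D = 0.2 baseline SD. The SD of D at 73 per arm is √(2/73) ≈ 0.165, so this is an ordinary imbalance. In units of the SD of change, s√(2(1 − r)), the shift is 0.2(1 − r)/√(2(1 − r)):

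- r = 0.5: 0.100, and 0.100/0.44 = 23% of the solid X effect
- r = 0.8: 0.063, and 0.063/0.44 = 14% of the solid X effect

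**The case against.** The strongest reply is that the plan is already valid. A comparison of change scores between randomized arms, adjusted for the minimization factors, is unbiased, with nominal type I error and coverage. That stands. A reader might infer from the omission that the treatment estimates are biased, but the documents do not support this. The shift in step 4 is conditional on one realised imbalance, averages to zero over randomization, and is already inside the change-score confidence interval. It is the same loss as in step 2 seen from another side, not a second defect.

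A reader might also infer that adjustment gains something at every r below 1. That needs equal pre and post variances, which the article does not report. In general, adjustment is never asymptotically worse, but the gain can be nil.

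The size rests on an undocumented r. The immediate endpoint compares tests just before and just after one treatment, so r near 0.9 cannot be excluded, and the gain is then about 2 points. Table 3 also uses no covariates, whereas the planned model has the minimization factors; any variance they explain may reduce the extra gain. Nor does it help everywhere: solid sway speed is already above 99%, and mean sway Y on foam stays badly underpowered (Power A, low end, 21% to 26.5% at r = 0.5).

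What does not stand is the reply that covariates are a detail for the analysis plan. The article names them, gives precision as the purpose of the second list, and leaves this one out.

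**Conclusion.** The point holds as one of avoidable imprecision. The primary model omits the BL2 pre-treatment value of its own outcome, and the variance penalty is 2/(1 + r) − 1: 33%, 11% and 5% at r of 0.5, 0.8 and 0.9. It is material for the contrasts that Table 3 puts below or near 80%, and small if r is about 0.9. The variance figures assume equal pre and post variances. The power figures further assume that the Table 3 SDs are SDs of change and that the minimization factors explain little of that change. The omission is certain from the text; the size is not, because r is not reported. It should be changed because the remedy is nearly free, not because the planned analysis is invalid.

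**What to change.** In each primary between-group model, for both the immediate and the 2-week endpoint, add the BL2 pre-treatment value of the same sway variable on the same surface as a prespecified continuous covariate, alongside the minimization factors. Do the same in the secondary between-group models that follow the primary method. Fix it in advance and do not place it among the covariates to be explored. Once it is in the model, the treatment contrast is the same whether the outcome is the change or the follow-up value.

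The cost is one sentence in the analysis plan and one degree of freedom per model. No new data are needed. Anyone with a change score from BL2 has the baseline value by construction, so no participant is lost under the article's rule against imputation. If the preliminary data allow it, report the pre/post correlation so that the gain can be stated and not assumed.
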